## Discussion

3

In the early stages of adhesive capsulitis, the aim of management is to alleviate pain so that rehabilitation can be used to restore normal shoulder range of motion and activity. Previous studies indicated that some patients could not finish rehabilitation because of the presence of intractable pain, leading to subsequent studies for investigating the effect of pain relief before rehabilitation. One of the most frequently used methods is intraarticular injection with a steroid. However, one review concluded that an intraarticular steroid injection before rehabilitation provided only a short-term benefit. Our study is the first to investigate the effect of PRF lesioning of the SSN plus physical therapy. The rapid onset of pain relief after PRF lesioning of the SSN apparently makes it easier for patients to tolerate rehabilitation therapy. However, more research is needed before we can recommend widespread adoption of this method as a treatment for adhesive capsulitis.

To our knowledge, there have been no published clinical trial to assess the synergistic effects of applying PRF stimulation of the SSN plus physical therapy on pain and function in patients with adhesive capsulitis. Therefore, we will conduct this present randomized, double-blind study to evaluate the synergistic effects of applying PRF stimulation of the SSN plus physical therapy on pain and function in patients with adhesive capsulitis. It is assumed that there will be a remarkable difference in postoperative outcomes between the intervention and control groups.

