**Methods::**

The study protocol is a randomized, controlled, double-blind design. Recruitment will be started in March 2021 and completed in October 2022. The treating surgeon will assess 90 patients for eligibility. The study protocol was approved through Institutional Review Board in the People's Hospital of Beilun district of Ningbo. Each patient will be randomized into 3 treatment groups, receiving PRF stimulation of the SSN or physical therapy or both of them. After baseline examination, all patients will be given a full explanation of the treatment protocol and will be required to sign a written informed consent for study participation and for publication of the results. All the data collectors, surgeons, statistical analysts, as well as result assessors are not aware of grouping assignment. The outcomes include Constant score, visual analog scale score, range of motion, and strength.

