Physical therapy agents including superficial and deep heat with analgesic currents are commonly used to decrease pain and spasm owing to adhesive capsulitis. Rehabilitation methods, including stretching, range of motion, strengthening exercises, and mobilization maneuvers are used to improve joint mobility and restore function. However, these interventions are usually painful and prevent the individual from fully participating in the rehabilitation program. Therefore, PRF lesioning of the SSN may be preferred for adhesive capsulitis before applying physical therapy.^[11,12]^

To our knowledge, there have been no published clinical trial to assess the synergistic effects of applying PRF stimulation of the SSN plus physical therapy on pain and function in patients with adhesive capsulitis. Therefore, we will conduct this present randomized, double-blind study to evaluate the synergistic effects of applying PRF stimulation of the SSN plus physical therapy on pain and function in patients with adhesive capsulitis. It is assumed that there will be a remarkable difference in postoperative outcomes between the intervention and control groups.

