### Physical therapy

2.5

Initially, hot pack application and transcutaneous electronic nerve stimulation are performed for groups. Then, for 12 weeks, stretching exercises, mobilization, and therapeutic exercises (30 min per session, 3 sessions per week) are performed under the guidance of a therapist who is blinded to patient allocation.

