### Outcomes parameters

2.6

All patients will be assessed for pain and functional status before and immediately after the treatment by a researcher blinded to the patient groups. The range of shoulder mobility and functional status will be assessed using the Constant Shoulder Scale, which was developed to evaluate functional recovery of the shoulder. The total Constant score ranges from 0 to 100 points, with higher scores indicative of better function. The score is divided into four sections: pain (15 points), activities of daily living (20 points), range of motion (40 points), and strength (25 points). Pain is scored using a visual analog scale. The activities of daily living score are divided into 4 subscales of sleep, work, recreational activities, and ability to position the hand in space. Range of motion is assessed in 4 active positions, with 10 points for each. Flexion and abduction are assessed by a goniometer, whereas functional internal and external rotation is assessed by the position of the hand. Strength is tested by a calibrated spring dynamometer, at 90° abduction of the shoulder with the forearm pronated and scored as the maximum of 3 repetitions (Tables 1 and 2).

**Table 1 T1:** Patient baseline demographics.

Demographics	Combined group	PRF lesioning of the SNN group	Ultrasound group	*P*
Number of patients (shoulders)				
Age, yr				
Male sex [no. (%)]				
BMI^∗^, kg/m^2^				
Left side [no. (%)]				
Follow-up^∗^				

BMI = body mass index, PRF = pulsed radiofrequency, SSN = suprascapular nerve.

∗ The values are given as the mean and the SD.

**Table 2 T2:** Postoperative outcomes.

Outcomes	Combined group	PRF lesioning of the SNN group	Ultrasound group	*P*
VAS				
Constant score				
Range of motion				
Muscle strength				

PRF = pulsed radiofrequency, SSN = suprascapular nerve, VAS = visual analog scale. The values are given as the mean and the SD.

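### The only post-baseline assessment is tied to the end of treatment, so patients who stop therapy early have no common assessment time

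*Protocol article*

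**What the plan says.** Section 2.6 (Outcomes parameters) gives the only assessment times: "All patients will be assessed for pain and functional status before and immediately after the treatment". Neither that section nor Tables 1 and 2 attach a week or date to the second assessment.

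Section 2.5 (Physical therapy) describes 12 weeks of supervised therapy at three sessions a week, that is 12 × 3 = 36 sessions. Section 2.4 describes the pulsed radiofrequency (PRF) treatment as one procedure with discharge after a short observation.

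Two passages bear on who will complete therapy. The Introduction says of rehabilitation methods that "these interventions are usually painful and prevent the individual from fully participating in the rehabilitation program". The Discussion adds: "Previous studies indicated that some patients could not finish rehabilitation because of the presence of intractable pain". It then says that pain relief from PRF "apparently makes it easier for patients to tolerate rehabilitation therapy".

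**The concern.** An assessment defined by the end of treatment has a clear time only for patients who reach that end. In a 12-week course that the protocol itself calls painful, some may not. The case for the combination is that PRF makes therapy more tolerable, so the protocol's own mechanism suggests that early stopping may be less common in the combined arm than with therapy alone.

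Patients who stop would then either be measured at a different time from completers or not be measured, and this could happen at different rates in the two arms. The combined versus therapy-alone contrast, which the question of added benefit depends on, would mix the treatment effect with the timing or absence of the final score.

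**Working it through.** **The plan's own figure.** Section 2.7 gives a 3 cm difference, SD 3.49, type I error 0.05 and power 0.8, and arrives at 25. Two-sided normal approximation: n = 2 × (1.96 + 0.842)² × 3.49² / 3² = 2 × 7.85 × 12.18 / 9 ≈ 21.2, so 22 per group. The two-sample t-test gives 22.2, so 23. Read as a per-group number, 25 is within two patients of the t-test result. This figure does not decide the present point; it supplies the SD and the target difference.

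**What the stated rule gives an early stopper.** There are two readings.

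1. *Treatment ends when the patient stops.* The final score is taken then, before completers are scored and possibly in pain. If early stopping is more common with therapy alone, the bias runs against therapy alone.
2. *Treatment ends only when the course is complete.* An early stopper never reaches the assessment and has no final score. If those who leave are the ones in more pain, the remaining therapy-alone patients look better than the randomised group.

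**Illustration for reading 2.** The documents give no dropout rate, so these inputs are assumptions: 30 per arm (90 split equally), normal pain outcomes with SD 3.49, a true difference of 3 cm in favour of the combination, a fraction q lost unassessed in therapy alone only, and a correlation ρ between the tendency to leave and a worse pain outcome. The apparent improvement in the therapy-alone mean is

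shift = ρ × SD × φ(z) / (1 − q),

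where z is the standard normal quantile at 1 − q and φ is the normal density. For example, with q = 10% and ρ = 0.3: 0.3 × 3.49 × 0.195 = 0.20 cm. Unrounded factors were used in the table. Pairwise power without loss is Φ(3 / (3.49 × √(2/30)) − 1.96) = Φ(3.33 − 1.96) = 0.91. Power with loss comes from a simulation using the completers' reduced SD and sample size.

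| Lost from therapy alone (q) | φ(z)/(1 − q) | Shift, ρ = 0.3 to 0.7 (cm) | Observed difference (cm) | Pairwise power |
|---|---|---|---|---|
| 10% | 0.195 | 0.20 to 0.48 | 2.80 to 2.52 | 0.86 to 0.81 |
| 20% | 0.350 | 0.37 to 0.85 | 2.63 to 2.15 | 0.80 to 0.67 |
| 30% | 0.497 | 0.52 to 1.21 | 2.48 to 1.79 | 0.72 to 0.50 |

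Any loss of the same kind in the combined arm would make the shift in the difference smaller.

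**Illustration for reading 1.** If a fraction q of therapy alone is scored at stopping, and those scores are on average D cm worse than they would have been on a common date, the arm mean worsens by q × D. The documents give nothing from which to estimate D. Borrowing 3 cm purely for scale, q of 10%, 20% and 30% gives 0.3, 0.6 and 0.9 cm, in the opposite direction. The two readings can therefore produce errors of similar order and opposite sign.

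**The case against.** **All patients are to be assessed.** Section 2.6 says so, and nothing limits assessment or analysis to completers. This stands. A reader might infer that pain-driven dropout would flatter therapy alone, or that a null result would have to be put down to selective loss. The document does not support either inference, because the text equally allows scoring at stopping, which pushes the other way. The signed-rank test in section 2.7 needs a baseline and a post-treatment value, so an unassessed patient would fall out of it, but that does not show that early stoppers will go unassessed. Promising to assess everyone still does not say when to assess someone who has left the course.

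**The wording may simply mean the end of the 12 weeks for everyone.** That is possible, and the repair would then only be to say so. The words do not point there naturally for a patient who stopped early, or for the PRF-alone arm, whose distinctive treatment is one procedure.

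**The premise is background.** The Discussion sentence concerns some patients in earlier studies, and limited participation, as the Introduction puts it, is weaker than stopping. This stands as a limit: no stopping rate is forecast for this trial. But the Introduction speaks in the protocol's own voice, and the rationale for the combination relies on better tolerance of therapy.

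**Handling of withdrawals, analysis populations and adherence records may sit in a full protocol or SAP.** This stands, and the point does not rest on their absence. Nor is the outcome list wrong: "The outcomes include Constant score, visual analog scale score, range of motion, and strength" matches the stated aim of pain and function. The cited patient-flow diagram, which is not shown, may count discontinuations, and Table 1 has rows by arm for number of patients and follow-up. It would be wrong to say that stopping goes unrecorded.

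**The sample has room for loss.** Ninety recruited against 3 × 25 = 75 leaves 15 patients, or 16.7%. That margin, which the article does not explain, would protect precision but would not remove a bias.

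**Conclusion.** The point holds as a defect in a stated rule: the one post-baseline assessment is anchored to the end of treatment, which gives early stoppers either a different assessment time or none, in a trial whose rationale expects tolerance of therapy to differ by arm. The direction of any bias cannot be determined from the document.

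Its size is also unknown. The 0.2 to 1.2 cm range, against a 3 cm target, applies only if early stoppers are not assessed, and it assumes 10% to 30% loss confined to therapy alone, a correlation of 0.3 to 0.7 with outcome, and normal scores on what is a bounded scale. A larger figure is tempting: if exactly the patients with the worst pain left (ρ = 1), the shifts would be 0.68, 1.22 and 1.73 cm. That is a ceiling under extreme selection and should not be read as an estimate.

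**What to change.** In section 2.6, replace the treatment-anchored timing of the second assessment with one fixed date counted from randomisation, the same for all three arms and for every randomised patient, whether or not therapy was completed. This removes both readings at once.

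The cost is a wording change and a call-back visit for patients who stop early. Recording sessions attended out of 36 and stopping because of pain, by arm, would be a useful optional addition because it would show whether tolerance of therapy did differ. Its absence is not an error in the plan.
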